## Abstract

**Background:**

More than 50% of patients with type 2 diabetes have hypertension in Uganda. Diabetic patients with elevated systolic blood pressure experience higher all-cause mortality and cardiovascular events compared with normotensive diabetic individuals, hence escalating resource utilization and cost of care. The aim of this study is to determine the effect of a nurse-led lifestyle choice and coaching intervention on systolic blood pressure among type 2 diabetic patients with a high atherosclerotic cardiovascular risk.

**Methods:**

This is a cluster-randomized study comprising two arms (intervention and non-intervention—control arm) with four clusters per arm with 388 diabetic patients with a high predicted 10-year atherosclerotic cardiovascular risk. The study will be implemented in 8 health facilities in Uganda. The intervention arm will employ a nurse-led lifestyle choice and coaching intervention. Within the intervention, nurses will be trained to provide structured health education, protocol-based hypertension management, and general atherosclerotic cardiovascular risk factor management, 24-h phone calls, and 2-monthly text messaging. The control group will be constituted by the usual care. The primary outcome measure is the mean difference in systolic blood pressure between the intervention and usual care groups after 6 months. The study is designed to have an 80% statistical power to detect an 8.5-mmHg mean reduction in systolic blood pressure from baseline to 6 months. The unit of analysis for the primary outcome is the individual participants. To monitor the effect of within-cluster correlation, generalized estimating equations will be used to assess the changes over time in systolic blood pressure as a continuous variable.

**Discussion:**

The data generated from this trial will inform change in the policy of shifting task of screening of hypertension and atherosclerotic cardiovascular disease from doctors to nurses.

**Trial registration:**

Pan African Trials Registry PACTR 202001916873358. Registered on 6 October 2019

## Administrative information

The order of the items has been modified to group similar items (see http://www.equator-network.org/reporting-guidelines/spirit-2013-statement-defining-standard-protocol-items-for-clinical-trials/).

## Introduction

### Background and rationale {6a}

By 2040, it is estimated that 642 million people will have type 2 diabetes worldwide while 1.39 billion people already have hypertension [1].

In Sub-Saharan Africa, hypertension affects younger age groups than in the developed world and is the major risk factor for heart failure, stroke, and kidney failure [2] This risk increases when one has diabetes.

In Uganda, the prevalence of hypertension is high ranging from 11 to 32% [3–7]. In a nationwide STEPS survey covering all major regions of the country with 3906 participants, the prevalence of hypertension was 26.4% [8].

More than 50% of patients with type 2 diabetes have hypertension [9].

Both conditions orchestrate cardiovascular disease [1, 2, 8]. There is a bi-directional relationship between diabetes and hypertension as patients with hypertension have insulin resistance and are at risk of developing diabetes in their lifetime [1].

The two conditions share similar pathophysiological pathways, namely endothelial dysfunction, vascular inflammation, arterial remodeling, atherosclerosis, dyslipidemia, and obesity [1, 9] Further analysis of Framingham data showed higher all-cause mortality, cardiovascular events in hypertensive diabetic patients compared with normotensive diabetics resulting from excessive atherosclerotic cardiovascular disease(ASCVD) risk [10].

A combination of diabetes and hypertension portends higher costs and resource utilization as this patient cohort suffers more myocardial infarctions and acute ischemic events, thus escalating the cost of care [9, 11]. In the USA, in a study by the National Health and Nutritional Survey (NHANES) 2005–2008, only 50% of hypertensive individuals had their blood pressure under control [12].

In Sub-Saharan Africa, the majority of patients have poorly controlled hypertension resulting from poor access to care and shortage of physicians [13].

In all the prevalence studies in Uganda, there are low rates of awareness of the condition among the patients [5, 6, 8, 14], resulting in low rates of treatment [4, 5], and control [2] leading to hypertension-related cardiovascular disease.

Among diabetic individuals, early landmark trials have demonstrated the benefits of strict BP control as it is associated with a reduction in heart failure and myocardial infarction (United Kingdom Prospective Diabetes Study (UKPDS) [15], Hypertension Optimal Treatment (HOT) [16], Systolic Hypertension in the Elderly (SHEP) [17], and Systolic Hypertension in Europe (Syst-Eur) [18]) though there is still controversy on the blood pressure target among type 2 diabetic patients.

Additionally, decreasing systolic blood pressure by 10 mmHg results in a 12% reduction of diabetes-related complications [19, 20].

Despite sufficient evidence for the benefit of hypertension control among type 2 diabetes, there is suboptimal control of blood pressure. In one systemic review of observational studies on treatment and blood pressure control in 47,964 people with diabetes and hypertension, control of blood pressure in patients with diabetes was suboptimal with less than 12% of patients achieving a blood pressure target of 130/80 mmHg [21].

In Sub-Saharan Africa, poor access to health care and physician shortage are the major hindrances to the control of hypertension [13].

In Uganda, control of hypertension among diabetic patients is still suboptimal as only 56% of them have their BP ≤ 140/80 mmHg [22].

A leading cause of suboptimal control of hypertension in Uganda is the lack of screening among patients with diabetes [22].

Other barriers to good blood pressure control are limited resources, ill-equipped health facilities, scarce medications, inadequate training of personnel, insufficient knowledge and experience of clinicians in the management of cardiovascular disease and hypertension, and lack of guidelines [23].

Diabetes and hypertension share similar risk factors such as insulin resistance, obesity, dyslipidemia, and endothelial dysfunction [1]. Effective control of both conditions requires a multifactorial approach. The STENO 2 trial demonstrated the benefit of multiple ASCVD risk factor management [24, 25].

Therefore, an intensive program that involves counseling about medical nutrition therapy, physical activity, smoking cessation, medication adherence, and behavior change with ongoing support and frequent follow-up are key for lifestyle management of weight, dyslipidemia, hypertension, and glycemia in patients with type 2 diabetes [25].

In the primary care setting, management of ASCVD and hypertension is done by doctors, but these are few [13] and spend less time with the patients; hence, there is a need to shift this task to other health care cadres such as nurses. There is evidence that nurses are traditionally well versed in self-care support and play a leading role in the administration of systematic educational interventions [26].

A systematic review of studies of nurse-led hypertension interventions in East Africa provided evidence that nurse-led interventions are effective in screening, diagnosis, and treatment of hypertension [27].

In one integrative review on nurse-led care interventions for high blood pressure control in Uganda, there was strong evidence to support nurse-led care interventions in the control of high blood pressure [28].

In Uganda, screening and management of ASCVD and hypertension among diabetic patients is a doctor’s role that takes place at health center IV, district, and regional referral hospitals, yet it is the nurses who spend most of the time with the patients and are readily available.

Therefore, the scarce doctors who are also involved in communicable disease care are stretched to provide timely and comprehensive ASCVD risk and hypertension screening and primary prevention in the community. This leads to patients presenting late with established cardiovascular disease for secondary care that is very expensive and fatal.

Improvement in diabetes, hypertension, and ASCVD care requires the transformation of the health system rather than a reactionary approach. Therefore, Wagner’s Chronic Care Model that improves care in health systems at community, organization practice, and patient levels will be adapted in this trial [29].

To our knowledge, no trial using the chronic care model has been conducted to study the effects of a nurse-led lifestyle choice and coaching intervention on systolic blood pressure among patients with type 2 diabetes with high ASCVD risk in Uganda.

### Objectives {7}

The aim of this study is to evaluate the effects of a nurse-led lifestyle choice and coaching intervention on systolic blood pressure and ASCVD risk factor profile among patients with type 2 diabetes. We hypothesize that a nurse-led lifestyle choice and coaching intervention reduces systolic blood pressure and ASCVD risk among type 2 diabetic patients with a high ASCVD risk.

### Trial design {8}

This is a cluster-randomized study with a parallel design in eight [8] diabetes clinics in the central region that usually refer patients with cardiovascular complications to Mengo Hospital as illustrated in Fig. 1. Consented patients with a high ASCVD risk score greater than 7.5% will be eligible for the study. The health facilities include Entebbe Grade B, Wakiso Health Centre IV, Kasangati Health Center IV, Mityana Hospital, Kawolo Hospitals, Mengo Hospital, Naguru Hospital, and Mpigi Health Center IV. These will form fixed clusters for randomization into intervention and control arms. Patients or the public were not involved in the study design.

**Fig. 1 Fig1:**
[figure not shown]
Study design. CVD, cardiovascular disease; ASCVD, atherosclerotic cardiovascular disease; LDL-C, low-density lipoprotein cholesterol

## Methods: participants, interventions, and outcomes

### Study setting {9}

Out of the 10 health facilities in Central Uganda that refer type 2 diabetic patients with cardiovascular disease to Mengo Hospital, eight [8] clinics which referred most patients in the preceding year were selected for the study. The facilities have nurses, clinical officers, and doctors who provide hypertension and ASCVD care with no formal treatment protocols. They were selected to allow for comparison between a nurse-led intervention and a usual care, which is only possible in health center IV and district hospitals. Eligible diabetic patients will be recruited from Entebbe Grade B Hospital, Mengo Hospital, Naguru Hospital, and Kasangati Health Center IV, which are urban health facilities, and Wakiso Health Center IV, Mpigi Health Center IV, Mityana Hospital, and Kawolo Hospital, which are peri-urban health facilities. These facilities run a weekly diabetes clinic where 50–120 patients are treated according to the size of the health facility. Approximately 250–600 patients with type 2 diabetes attend these clinics per week. The facilities have well-organized manual patients’ registers. Thus, intervention in these facilities will be handy in the prevention and management of hypertension and ASCVD among patients with type 2 diabetes.

### Eligibility criteria {10}

The inclusion criteria for study health facilities are as follows:
The study health facility must be running a regular outpatient diabetes clinic.Must be located in an urban or peri-urban area in the central region.The diabetes clinic must be having at least 85 outpatient visits per week to ensure the recruitment of enough participants.The minimum distance between health facilities should be more than 6 km to minimize contamination.The health facilities should not share health professionals to minimize intervention bias.The diabetes clinic must be run by nurses and clinical officers or medical officers with well-maintained records and dispensary.

The eligibility criteria for study participants are as follows:
Inclusion criteria:Adult men and women with type 2 diabetes aged 40–79 years with a high ASCVD risk score of at least 7.5% as calculated with the pooled cohort risk equationsWilling to provide informed consentAsymptomatic for ASCVD (those without a history of non-fatal myocardial infarction, stroke, heart failure, percutaneous coronary intervention, coronary artery bypass surgery, or current atrial fibrillation)Exclusion criteria:
Pregnant women (pooled cohort equation has not been validated in pregnancy)Those with other comorbidities such as chronic kidney disease and liver diseasePatients who do not usually keep appointments, that is, those who have attended clinics only once per year

### Who will take informed consent? {26a}

After confirming eligibility, trained study nurses will obtain written informed consent from potential participants.

### Additional consent provisions for collection and use of participant data and biological specimens {26b}

Blood will be collected, but it will not be used for genetic and molecular analysis in this trial and future.

## Interventions

### Explanation for the choice of comparators {6b}

Out of the 10 health facilities in Central Uganda that refer type 2 diabetic patients with cardiovascular disease to Mengo Hospital, eight [8] clinics which referred most patients in the preceding year were selected for the study. The facilities have nurses, clinical officers, and doctors who provide hypertension and ASCVD care with no formal treatment protocols. Health center IV and above were selected to allow for comparison between a nurse-led intervention and a usual care, which is only possible in health center IVs and district hospitals.

### Intervention description{11a}

#### Nurse-led lifestyle change education and management at the health facility

The purpose of this trial is to evaluate the effects of a nurse-led lifestyle change education, management, and coaching intervention on systolic blood pressure among patients with type 2 diabetes with a high ASCVD risk score of at least 7.5% as determined by the pooled cohort risk equations. The intervention will be targeted at both cluster (group) and individual levels. The clusters will be allocated in a 1:1 ratio between intervention and usual care arms.

Our intervention is based on Wagner’s Chronic Care Model (CCM) as shown in Fig. 2. Wagner’s Chronic Care Model is the best-evidenced strategy to improve diabetes outcomes in the primary care setting [29]. The CCM gives a conceptual framework for reorganizing care from the acute reactive system to a population-based proactively planned care of patients with chronic illnesses such as diabetes, hypertension, and ASCVD [30].

**Fig. 2 Fig2:**
[figure not shown]
The study conceptual framework. Adapted from Wagner’s Chronic Care Model [29]. HT, hypertension; ASCVD, atherosclerotic cardiovascular disease

Participants in the intervention group will be subjected to the Nurse-led lifestyle change education, management, and coaching intervention which comprised two components. The first component is the facility-based nurse-led lifestyle change education that is cluster-based, protocol-led hypertension and ASCVD management and treatment adherence counseling that is individualized. The second component is the individualized home-based coaching support.

#### Nurse-led lifestyle change education and management at the health facility

Two nurses from each facility will be identified and trained for 1 day at the study head office in Mengo Hospital. The training will aim to enhance the capacity of the nurses to screen and manage hypertension and ASCVD. They will be trained on ASCVD risk factor assessment with the pooled cohort risk equations, initiation of treatment for hypertension and ASCVD, when and where to refer, and principles of health promotion and behavioral change.

At the end of the training, the nurses will be able to provide group structured health education on ASCVD prevention and management.

The health education sessions will last 30 min, and they will be conducted every 2 months for 6 months. The participants will be educated on the relationship between ASCVD and diabetes, risk factor management, and benefits of medication adherence. The education sessions will be followed by a 15-min question and answer session where participants will be allowed to ask questions. The participants will be provided with an ASCVD leaflet that will be published in both English and the local language. The leaflet will be provided once at the beginning of the trial, but they will be encouraged by the study nurses to come with it every time they come to the health education. The purpose of health education is to produce an informed proactive patient. Improvement in participants’ behavior will be shown with treatment adherence rates and lifestyle change testimonies during sessions. During sessions, participants will elect a leader (peer leader) who will be trained by the study nurses to help in coordinating health education sessions and referral of the critically ill from the community to the health facility.

The nurses will provide protocol-based hypertension and ASCVD management as shown in Fig. 3. The protocol has been developed by the principal investigator. The protocol will be used to guide the management and provision of medicine (i.e., lipid-lowering agents, anti-hypertensives). The protocol will give clear guidance on how to determine patient stability and when to refer to a clinical or medical officer in the respective facility or a facility higher. This strategy underpins the task shifting of hypertension and entire ASCVD management from a clinical or medical officer to a well-trained and facilitated nurse with a well health-educated, informed, and supported patient at the center. Therefore, improvement in this capacity will be assessed by the number of patients on appropriate anti-hypertensives, lipid-lowering agents, and referrals.

**Fig. 3 Fig3:**
[figure not shown]
Protocol for ASCVD and hypertension management. ASCVD, atherosclerotic cardiovascular disease

### Coaching intervention

The second component of the intervention will be the coaching support where individual participants in the intervention group will be given support at home. The study nurses will make individualized telephone calls, send text messages, and operate a 24-h mobile telephone service to answer study participants’ questions and concerns. The phone calls will be structured along the health education topics provided at the health facility. It is anticipated that telephone calls will last for 7 min per participant. Thus, for 194 participants, 22 h of calls will be consumed each time the study participants are called. Participants will be called 3 times during the entire trial period. The participant and the areas discussed will be registered in the call log. Text messages will be sent every after 2 months. The messages will contain topics discussed during the health education talks and in the leaflet. Every time messages are sent, they will be recorded in the text messages’ log.

The telephone calls and text messages will reinforce individualized hypertension and ASCVD management plan at home. The nurse-patient relationship which is key in the chronic disease care model will be strengthened through calls and text messages. The intervention components are as shown in Fig. 4.

**Fig. 4 Fig4:**
[figure not shown]
Intervention components. HT, hypertension; ASCVD, atherosclerotic cardiovascular disease; VHT, Village Health Team. 176 × 135 mm (300 × 300 DPI)

### The usual hypertension/ASCVD care

The control group of the study will comprise the usual care that is the doctor- or clinical officer-led at health centers IV and higher where either patients are referred by nurses or refer themselves with symptoms of ASCVD. In the usual care, patients with diabetes are not subjected to ASCVD risk quantification. Nurses give general health education on diabetes self-care practice which is not structured along with primary hypertension and ASCVD prevention and management. Health education does not build a nurse-patient relationship with a well-educated motivated patient at the center. All patients are given the same management package irrespective of their risk factor profile. Management of hypertension and ASCVD in the health facilities in Uganda is not protocol-based as every facility manages diabetes and hypertension differently. Apart from the general Information Education Communication materials at the clinics, patients are not given information leaflets and are not followed with phone calls and text messages and neither can they call the health workers any time of the day. Patients are followed only in the clinics when they are given review appointments by the doctors or clinical officers. Nurses in these facilities have varied training and skill in diabetes management.

### Criteria for discontinuing or modifying allocated interventions {11b}

Given the fact that the intervention components are some of the routine procedures at the clinics, we anticipate low risk. However, if a participant opts out, or develops an adverse event, she or he will be discontinued from the study.

### Strategies to improve adherence to interventions {11c}

To reduce dropout rates, participants in the intervention arm will be receiving a transport refund. The two monthly calls that are part of the motivation component will also be used to encourage participants to attend follow-up visits. The follow-up log will be used to register visits and also establish those defaulting and their reasons for not attending.

### Relevant concomitant care permitted or prohibited during the trial {11d}

The participants in both intervention and control arms will continue receiving hypertension, diabetes, and ASCVD treatment as deemed appropriate by the health workers in these facilities. The care in the intervention arm will be provided by the trained study nurses according to the study protocol. The care in the control arm will be the usual management provided by the medical officers, clinical officers, and nursing officers.

### Provisions for post-trial care {30}

After the trial, all participants irrespective of their randomization will continue with care in their facilities. The results from the trial will be shared with all the health facilities. Any finding that imparts on treatment outcomes will be shared. Our trial is a low-risk study, and we anticipate low rates of harm. However, in case of an anticipated adverse event, standard operating procedures will be followed.

### Outcomes {12}

#### Primary outcomes

The primary outcome of the trial will be the mean difference in the change in systolic blood pressure between baseline and 6 months between the intervention and usual care groups at individual and cluster levels.

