### Sample size {14}

To detect an 8.5-mmHg mean difference in systolic pressure between the intervention and control arms, the sample size was calculated basing on a study by Rudd et al. [31]. The study evaluated the effects of a nurse-led use of algorithm-based prescribing compared to usual care where there was a mean change in systolic blood pressure of 14.2 mmHg (standard deviation (SD) = 17.2) in the intervention arm and 5.7 mmHg (SD = 18.7) in the control arm [31].

To have an 80% power for the trial at a significance level of 0.05, a 2-tailed test assuming an intracluster correlation coefficient (ICC)of 0.035 for continuous clinical outcomes for studies related to cardiovascular disease and management in primary care practices [32] has been used. Given that we shall have 4 fixed clinics (clusters) per arm, the sample size for each arm has been calculated using the formula for a fixed number of equal-sized clusters as described by Hemming et al. [33]. The sample size for each arm will be 174. Assuming a 10% loss to follow-up over the 6 months, the final sample size for each arm will be 193.3 rounded to 194 with each cluster having 49 participants. We recognize that the study may not be powered enough for the secondary outcomes since the sample size has been calculated based on the primary outcome.

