## Statistical methods

### Statistical methods for primary and secondary outcomes {20a}

Participant characteristics will be described using simple descriptive characteristics. We will use the mean and standard deviation to describe normally distributed continuous variables and the median and upper and lower limits of the interquartile range to describe non-normally distributed continuous variables. Normality of continuous variables will be assessed by visual inspection of histograms. Categorical data will be presented in counts and percentages.

Data will be analyzed according to the intention-to-treat (ITT) principle.

The primary outcome of the trial is the mean difference in the change in systolic blood pressure between baseline and 6 months and between the intervention and usual care groups at individual and cluster levels. It will be expressed as the mean systolic blood pressure difference between the groups (with 95% CI).

This value will be measured as the difference between matched diabetes clinics (intervention clinics minus control clinics) in systolic blood pressure (systolic blood pressure in the intervention period minus systolic blood pressure in the baseline period). The hypothesis for this study is that a nurse-led lifestyle choice and coaching intervention reduces systolic blood pressure compared to usual care among type 2 diabetic patients with high ASCVD risk.

In this study, the same individuals will be assessed at baseline and follow-up (cohort design), and analysis of covariance (ANCOVA) will be used to analyze each individual’s outcome at follow-up adjusted for that individual’s outcome at baseline with mixed-effects linear regression or generalized estimating equations to assess changes over time in systolic blood pressure as a continuous variable between clusters [36, 37]. A random intercept representing each cluster will be added to each model to account for the intra-cluster correlation (ICC). We shall adjust the analysis models by the balancing factor urban or peri-urban.

Appropriate analyses will be employed to assess the secondary outcomes between study arms. Since sample size calculation for the trial was based on the primary outcome, the lack of significant differences between the arms may be due to the true lack of differences or due to inadequate power. Therefore, secondary outcome interpretation will be cautiously done.

All analyses will be conducted using the SPSS software version 25.

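### The primary outcome is set at two levels and tied both to a matched-clinic change difference and to an individual-level ANCOVA, without saying which carries the 5% test

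*Protocol article*

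**What the plan says.** Four places in the protocol article bear on the primary analysis.

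- **Outcomes {12}, Primary outcomes.** The outcome is placed at two levels: "mean difference in the change in systolic blood pressure between baseline and 6 months between the intervention and usual care groups at individual and cluster". The statistical methods section {20a} repeats this two-level definition.
- **Statistical methods {20a}, definition of the value.** "This value will be measured as the difference between matched diabetes clinics (intervention clinics minus control clinics) in systolic blood pressure", taken as intervention period minus baseline period. This is a clinic-level contrast of changes.
- **Statistical methods {20a}, following paragraph.** ANCOVA will be used to "analyze each individual’s outcome at follow-up adjusted for that individual’s outcome at baseline", by mixed-effects regression or GEE, with a clinic random intercept and adjustment for urban or peri-urban location. This is an individual-level contrast of follow-up values.
- **Abstract, Methods.** "The unit of analysis for the primary outcome is the individual participants". The outcome is given there as the "mean difference in systolic blood pressure between the intervention and usual care groups after 6 months", with no change from baseline in that sentence.

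Sample size {14} sets one error rate and one power: "To have an 80% power for the trial at a significance level of 0.05, a 2-tailed test". It is based on standard deviations of individual change and an ICC, and uses neither pairing nor baseline adjustment.

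**The concern.** The matched-clinic sentence says how the primary value is obtained, and the ANCOVA sentence says how it is analysed. They do not describe the same calculation. A random-intercept ANCOVA with an urban/peri-urban term does not yield a difference between matched clinics, and a matched-clinic difference in change is not adjusted for baseline by regression. An analyst cannot follow both sentences and report one primary result, and the text gives no order of precedence.

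With only four clinics per arm this matters. The contrasts differ little in what they estimate but a good deal in precision and degrees of freedom, so whether the trial is called positive can depend on which one is read out. The stated 5% error rate and 80% power are not attached to a particular statistic.

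**Working it through.** **Inputs from Sample size {14}.** Difference 8.5 mmHg; SD of change 17.2 and 18.7; ICC 0.035; 4 clinics per arm; two-sided 0.05; power 80%; 10% loss; 49 per clinic.

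**The plan's own figure.**
- SD = √((17.2² + 18.7²)/2) = 17.97.
- Individually randomised n per arm = 2 × (17.97 × (1.960 + 0.842)/8.5)² = 70.1.
- For a fixed number of equal clusters, m = n(1 − ICC)/(k − n·ICC) = 70 × 0.965/(4 − 2.45) = 43.6 per clinic, so 174 per arm.
- 174/0.9 = 193.3, rounded to 194.

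The stated sizes reproduce, so the sample-size arithmetic is not at issue.

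**Assumptions added.** 44 evaluable per clinic (49 × 0.9 = 44.1). Four intervention-control pairs; the pairing sentence in Sequence generation {16a} is not clear on this. Baseline-to-follow-up correlation r = 0.3, 0.5 or 0.7, the same between and within clinics; the protocol gives none. No extra correlation within pairs.

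**Standard errors.**
- Change difference: 17.97 × √(2 × (1 + 43 × 0.035)/(4 × 44)) = 3.03 mmHg.
- ANCOVA: the residual variance is (1 + r)/2 times the change variance, so SE = 3.03 × √((1 + r)/2) = 2.44, 2.63 and 2.79 mmHg for r = 0.3, 0.5 and 0.7.

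**Estimate needed for significance, if the SE comes out at its expected value.**
- Matched clinics, 3 df: 3.18 × 3.03 = 9.6 mmHg, which is larger than the 8.5 mmHg planned for.
- ANCOVA, 5 df (8 clinics less intercept, arm and stratum): 2.57 × 2.44 = 6.3 up to 2.57 × 2.79 = 7.2 mmHg.

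**Power at 8.5 mmHg (noncentral t).** With a normal reference and SE 3.03, power is 80%, which is the plan's basis. The alternatives, with simulated agreement between the two tests, are:

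| | r = 0.3 | r = 0.5 | r = 0.7 |
|---|---|---|---|
| Matched clinics, 3 df | 48% | 48% | 48% |
| ANCOVA, 5 df | 79% | 74% | 68% |
| Verdicts on significance differ | 36–37% | 32% | 28% |
| No effect: either test significant | 8.6% | 8.3% | 7.9% |

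Repeat simulations agree to about one percentage point. In the r = 0.5 column, with no effect, each test rejects in about 5.0% and they disagree in 6.6%, so either rejects in (5.0 + 5.0 + 6.6)/2 = 8.3%.

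**Direction.** In model-based simulations at a true 8.5 mmHg reduction, mean estimates were about −8.3 to −8.6 mmHg for every version. Having both tests significant in opposite directions was essentially never seen.

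**The case against.** The text leans one way. The abstract names the individual as the unit, the sample size is built from individual change with an ICC, and ANCOVA is the only named method for the primary outcome. The two-level phrase could be a loose description of a multilevel model, and the matched-clinic sentence could merely fix the direction of subtraction; it names no test, degrees of freedom or decision rule. The paired test on 3 df is therefore a construction, and its lower power is what one expects of a low-df test. All of that stands and limits the size of the point. It does not remove the conflict: the two-level definition appears twice, the matched-clinic sentence is worded as a definition, and an analysis plan that chose one contrast would still leave the published text contradicting itself.

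Three stronger readings are not supported.

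- A reader might infer opposite conclusions in the sense of benefit against harm. The disagreement is between significant and not significant only.
- A reader might infer that the trial's error rate is already inflated. That needs a rule that success on any version counts, and no section states one. The blinding of the analysing statistician also lowers the risk of choosing after the fact, though it does not name a contrast.
- A reader might count changes over time as a further contrast. With measurements only at baseline and 6 months it is not a separate one, and {20a} uses the phrase inside the ANCOVA sentence.

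It is also fair that naming a random-intercept ANCOVA does not by itself secure 5%. With an uncorrected normal reference, simulated false-positive rates for that model were 7–10%, so the fix has to include the reference distribution.

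**Conclusion.** The point holds as an internal contradiction in the protocol article that should be corrected before the data are analysed. The primary outcome is placed at two levels and given both a matched-clinic and an individual-level form, and no sentence assigns the single two-sided 5% test to either. The choice is worth roughly 20 to 31 percentage points of power (48% against 68–79%) and changes the verdict on significance in about 28–36% of trials at the planned effect. The 8% false-positive rate is conditional on claiming success on either test. These sizes depend on the assumed four pairs, equal clinics of 44, and a correlation of 0.3 to 0.7; the contradiction itself does not depend on them.

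**What to change.** In Outcomes {12} and Statistical methods {20a}, delete the words that place the outcome at both individual and cluster level, and delete the sentence that measures the value between matched clinics. Replace them with one statement along these lines:

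> The primary contrast is the adjusted mean difference (intervention minus usual care) in systolic blood pressure at 6 months, from an individual-level ANCOVA with baseline systolic blood pressure, the urban/peri-urban factor and a clinic random intercept. It is tested once at two-sided 0.05, using a t reference with cluster-based degrees of freedom (about 5 for 8 clinics).

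Label the matched-clinic difference and the unadjusted difference in change as supportive sensitivity analyses that cannot alter the primary conclusion. Align the abstract's outcome sentence with this wording.

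The cost is wording only: no added patients, visits or data. The sponsor gives up the option of claiming success at the other level, and the small-sample reference gives a somewhat wider confidence interval than a normal one.
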